#### Assessment of performance

The model’s performance will be assessed using temporal validation, a type of internal validation. Whereas internal validation using random splitting or resampling (i.e., bootstrapping, cross-validation) evaluates reproducibility, it does not evaluate transportability. In contrast, temporal validation evaluates transportability since the cohort is temporally distinct from the derivation cohort [69–71].

The final model’s performance will be assessed and reported using measures of predictive accuracy, discrimination, and calibration in the validation cohort. Predictive accuracy will be measured by means of Nagelkerke’s *R*^*2*^[72]. Discrimination represents the model’s ability to distinguish between those who have and those who do not have the outcome. It will be measured using the c-statistic, which is equivalent to the area under the receiver operating characteristic curve when the outcome is binary. Calibration represents the model’s ability to generate predictions of the probability of death that mirror the observed probability of death. It will be assessed visually by means of a calibration plot, generated by regressing the outcome variable on the predicted risk of mortality. The slope and intercept of the calibration curve will be calculated; a model with a slope of 1 and intercept of 0 is perfectly calibrated. The clinically relevant standard of calibration is defined as less than a 20% difference between observed and predicted probabilities with an event rate of at least 5% [73]. Calibration will also be evaluated within predefined subgroups of importance to clinicians and policymakers (e.g., groups defined by age, sex, living status, and comorbid disease). Calibration will not be assessed via statistical means, namely the Hosmer–Lemeshow statistic, since it has been shown to perform poorly in large samples [38] and to have insufficient power to detect overfitting [39].

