**Methods:**

The derivation cohort will include approximately 235,000 patients with dementia, who were admitted to hospital in Ontario from April 1st, 2009, to December 31st, 2017. Predictor variables will be fully prespecified based on a literature review of etiological studies and existing prognostic tools, and on subject-matter expertise; they will be categorized as follows: sociodemographic factors, comorbidities, previous interventions, functional status, nutritional status, admission information, previous health care utilization. Data-driven selection of predictors will be avoided. Continuous predictors will be modelled as restricted cubic splines. The outcome variable will be mortality within 1 year of admission, which will be modelled as a binary variable, such that a logistic regression model will be estimated. Predictor and outcome variables will be derived from linked population-level healthcare administrative databases. The validation cohort will comprise about 63,000 dementia patients, who were admitted to hospital in Ontario from January 1st, 2018, to March 31st, 2019. Model performance, measured by predictive accuracy, discrimination, and calibration, will be assessed using internal (temporal) validation. Calibration will be evaluated in the total validation cohort and in subgroups of importance to clinicians and policymakers. The final model will be based on the full cohort.

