#### Model estimation

The model will be estimated using a binary logistic regression. All predictor variables will be centered about their means. Multi-collinearity will be assessed using variable clustering using the VARCLUS function in SAS [67]. In addition, the variance inflation factor (VIF) will be calculated for each predictor variable. Predictors with a VIF > 2.5 will be judged to be potentially collinear. These methods will be used to understand the model with more clarity though will not result in further model specification.

Overfitting will be assessed visually using the calibration plot (see Assessment of performance), and statistically using the heuristic shrinkage estimator [68]. If the estimator is less than 0.9, then this suggests the presence of overfitting that requires adjustment, including shrinkage of the parameter estimates. This is unlikely considering prespecification of the model, and the low number of degrees of freedom in the model relative to the high number of events in the cohort. We intend to have the model provide an automatic calculation of mortality risk, not to have it used manually to calculate risk (see Model presentation). Therefore, predictive accuracy will be prioritized over parsimony, and a reduced model will not be estimated.

The model will be developed and validated using temporally split samples; however, the final regression coefficients will be based on the full sample. The final model will have the same specifications as the derivation model.

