## Discussion

### Model presentation

The final regression model, based on the total cohort, will be presented using beta coefficients and corresponding standard errors.

The regression formula of the model will be disseminated on a publicly accessible website, www.projectbiglife.com, which houses existing clinical prediction tools developed by our team. Because of the complexity of the model, the tool will not be used manually. Rather, it will be integrated into the electronic medical records of hospitals, such that the risk of 1-year mortality will be automatically calculated by the computer upon admission. For example, upon admission, based on routinely collected information in a hospital’s data warehouse, the risk of 1-year mortality will be automatically calculated for a patient with dementia. If the risk exceeds a threshold, then the admitting team will be alerted. The threshold will be based on the capacity of medical, surgical, and specialist palliative care teams to provide care (e.g., a high threshold if the teams have a limited capacity). Equipped with and impelled by this information, they will be able to engage in discussions about goals of care (primary palliative care) or make a referral to the specialist team if needs are complex (Fig. 1). This implementation is similar to that of the mHOMR in Ontario.

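### The sentence that sets the validation measures names the final model, which the protocol elsewhere defines as the full-cohort refit containing the validation patients

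*Protocol article*

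**What the plan says.** The protocol article says in three places what the final model is:

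- Abstract, Methods: "The final model will be based on the full cohort".
- Model estimation: "The model will be developed and validated using temporally split samples; however, the final regression coefficients will be based on the full sample". The next sentence adds: "The final model will have the same specifications as the derivation model".
- Model presentation: "The final regression model, based on the total cohort, will be presented using beta coefficients and corresponding standard errors".

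Assessment of performance opens with the design: "The model’s performance will be assessed using temporal validation, a type of internal validation". It justifies that choice on the ground that "temporal validation evaluates transportability since the cohort is temporally distinct from the derivation cohort". The sentence that fixes what is reported then reads: "The final model’s performance will be assessed and reported using measures of predictive accuracy, discrimination, and calibration in the validation cohort".

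**The concern.** By the article's own definition, the final model is fitted to derivation and validation patients together. A sentence that assesses this model in the validation cohort therefore tests an equation on some of the patients who shaped it. The article has a separate term for the other candidate, the derivation model, but does not use it here.

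Three things depend on which coefficients are meant.

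- The case for temporal validation is that the two cohorts are distinct in time. That does not hold for coefficients estimated on both.
- The Background criticises earlier tools for weak assessment of calibration, and the Objectives present calibration as an advance. Drift over time shows directly in calibration, and a refit absorbs part of it.
- Model estimation uses the same calibration plot as a visual check for overfitting. On the literal reading that check would also include fitting data.

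Readers also need to know whether the reported c-statistic, slope and intercept belong to the published equation or to another set of coefficients.

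**Working it through.** **Inputs** (Sample size section; counts are approximate): derivation 235,000 patients and 82,000 deaths; validation 63,000 patients and 21,000 deaths; total 298,000. The minimum-sample-size inputs are c = 0.77, event proportion 0.35, 205 parameters and shrinkage 0.90, with a stated result of 8251.

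**1. The plan's own figure.** A Cox-Snell R² of about 0.199 was simulated from c = 0.77 and prevalence 0.35. The shrinkage criterion n = P / [(S − 1) ln(1 − R²/S)] then gives 205 / [(−0.1) × ln(1 − 0.1992/0.9)] ≈ 8,195. This is within 1% of 8251, so the figure reproduces and the R² can be reused in step 4.

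**2. Share of the validation cohort in the refit.** 63,000/298,000 = 21.1%. The other 78.9% of the fitting data lies outside the validation cohort.

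**3. Effect on overall calibration, from the stated counts.**

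- Event proportions: derivation 82/235 = 0.3489; validation 21/63 = 0.3333; full cohort 103/298 = 0.3456.
- A logistic model with an intercept reproduces the event proportion of its fitting sample. If case-mix is constant, that proportion is also the mean predicted risk in the validation cohort.
- Observed/expected (O/E) with derivation coefficients: 0.3333/0.3489 = 0.955.
- O/E with full-cohort coefficients: 0.3333/0.3456 = 0.964.
- Share of the gap absorbed: (0.3489 − 0.3456)/(0.3489 − 0.3333) = 0.21.

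If each count is rounded to the nearest thousand, the two ratios could be as low as 0.918 and 0.934 or as high as 0.994 and 0.995. The difference between them is then 0.001 to 0.016.

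**4. Optimism from overfitting.** Heuristic shrinkage is (χ² − df)/χ², with χ² = −n ln(1 − R²).

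- n = 235,000: χ² ≈ 52,200; shrinkage = 0.996.
- n = 298,000: χ² ≈ 66,200; shrinkage = 0.997.

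Both are far above the plan's 0.9 trigger.

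**5. Illustration with an assumed drift.** A small simulation (205 parameters, the stated cohort sizes, two replicates, so subject to noise) scored the validation cohort with both sets of coefficients.

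| Scenario | Measure | Derivation only | Full refit |
|---|---|---|---|
| No drift | c | 0.7625 | 0.7635 |
| No drift | slope | 0.978 | 0.987 |
| Assumed drift | c | 0.747 | 0.752 |
| Assumed drift | slope | 0.888 | 0.936 |
| Assumed drift | O/E | 0.925 | 0.940 |

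The assumed drift lowered the intercept from −0.76 to −0.90, scaled the coefficients by 0.9 and added random changes to them. It is an assumption and comes from nothing in the article. In that scenario the refit closes (0.940 − 0.925)/(1 − 0.925) = 20% of the O/E gap, in line with step 3. It closes (0.936 − 0.888)/(1 − 0.888) = 43% of the slope gap, so the one-fifth figure applies to overall calibration only.

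**The case against.** The strongest reply is that the article already describes the right sequence. Model estimation says that development and validation use split samples, and only after the word *however* turns to the full-sample coefficients. It also refers to a derivation model as a separate object. Assessment of performance opens with temporal validation, and the Abstract places the full-cohort model after the validation step. Model specification uses *final model* more loosely, for the model after degrees of freedom have been reallocated, and the disputed sentence can be read in that sense. All this stands, and it makes the derivation model the likelier intent. It does not make the sentence correct: a term used in two senses leaves open which coefficients produce the headline results.

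A reader might go further and infer that the reported validation would simply be resubstitution, or that the transportability evidence fails. The article does not support that. It follows only if one noun phrase overrides the rest of the design, and even then 79% of the fitting data lies outside the test cohort.

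It is also fair to reply that the size is small. Both O/E values from the stated counts lie within 5% of 1, against the article's 20% calibration standard, so the overall judgement would not change.

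Finally, refitting on all data after a split-sample validation is legitimate and openly stated, and the article requires external validation before implementation. The absence of a held-out estimate for the refit is therefore something to state, not an error.

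**Conclusion.** The article contradicts itself on which model is assessed in the validation cohort, and the sentence that fixes the reported measures is wrong as written. If it were followed literally, 21% of the fitting data would be the test data. About one fifth of any drift in overall event risk would then be hidden: O/E 0.964 instead of 0.955, assuming constant case-mix and taking the rounded counts at face value. Overfitting adds almost nothing (heuristic shrinkage about 0.996). Larger effects on the slope or c-statistic depend on a drift size that the article does not give. Because the derivation model is probably intended and the effect on the stated counts is small, severity is low to moderate. The correction still matters, because temporal validation is there to expose the drift that the literal reading would dilute.

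**What to change.** In Assessment of performance, change the subject of the sentence from the final model to the derivation-cohort model. State that R², the c-statistic and calibration, overall and by subgroup, use coefficients, knot positions, centering values and degrees-of-freedom decisions from the derivation data only. Add one sentence, there or under Model presentation, saying that the published full-cohort equation has the same specification but no held-out validation of its own.

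This costs one or two sentences and needs no new data or change in sample size. Internal-external or bootstrap-corrected performance for the refit, labelled as such, is optional.

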## Discussion

### Model presentation

The final regression model, based on the total cohort, will be presented using beta coefficients and corresponding standard errors.

The regression formula of the model will be disseminated on a publicly accessible website, www.projectbiglife.com, which houses existing clinical prediction tools developed by our team. Because of the complexity of the model, the tool will not be used manually. Rather, it will be integrated into the electronic medical records of hospitals, such that the risk of 1-year mortality will be automatically calculated by the computer upon admission. For example, upon admission, based on routinely collected information in a hospital’s data warehouse, the risk of 1-year mortality will be automatically calculated for a patient with dementia. If the risk exceeds a threshold, then the admitting team will be alerted. The threshold will be based on the capacity of medical, surgical, and specialist palliative care teams to provide care (e.g., a high threshold if the teams have a limited capacity). Equipped with and impelled by this information, they will be able to engage in discussions about goals of care (primary palliative care) or make a referral to the specialist team if needs are complex (Fig. 1). This implementation is similar to that of the mHOMR in Ontario.

**Fig. 1 Fig1:**
[figure not shown]
**A** A patient with dementia is hospitalized, at which point a risk of 1-year mortality is automatically calculated by the computer. **B** If the risk of mortality is below a user-defined threshold, then the admitting team is not alerted. The threshold is based on the capacity of medical and specialist palliative care teams to act on the alert. **C** If the risk of mortality is above the threshold, then the admitting team is alerted. **D** The alert could prompt the admitting team to initiate advance care planning (primary palliative care). **E** The alert could prompt the admitting team to refer to specialist palliative care if needs are complex

### Contribution of this study

This tool has the potential to inform health policy, research, and clinical practice. First, it could inform eligibility criteria for specialist palliative care services, including those for hospice. These criteria, which are usually based on functional status and estimated prognosis, may presently be restrictive to patients with dementia and other non-malignant diseases [74], which are characterized by an undefined “terminal” phase of disease [75]. For example, a tool that was intended to predict 6-month mortality among nursing home residents with advanced dementia [76] performed better than Medicare hospice eligibility guidelines [77]. This demonstrates the potential limitations of the rules that presently govern how palliative care is accessed, and the promise of a prognostic tool to mitigate these limitations by more sufficiently informing the decision to access palliative care. Second, the tool could identify cohorts of patients with dementia that could most benefit from palliative care interventions. This could facilitate a more targeted selection of participants in both research trials and quality improvement initiatives.

Finally, the tool could minimize the barrier of prognostic uncertainty [75, 78–80] of hospitalized patients with dementia to palliative care. That is, if a patient is found to have a high risk of 1-year mortality, then this could prompt their provider to pursue palliative care. This would appear to go against the widely accepted knowledge that the pursuit of palliative care be based on needs rather than on prognosis [81, 82]. In practice, a prognostic tool would not supplant the needs-based approach but would complement it. For example, a clinician who identifies palliative care needs in a patient with dementia, paralyzed by prognostic uncertainty and falsely reassured by the possibility of “more time” [80], may not refer to specialist palliative care. A prognostic tool that identifies the patient as high risk for mortality could empower the clinician to do so. In concert, the assessment of needs and the estimation of prognosis would identify patients who require specialist palliative care intervention most urgently; this approach would accommodate the current limitations in the capacity of specialist palliative care providers to deliver services en masse.

### Limitations

We sought to include primarily predictor variables available in the DAD. Though this database includes the vast majority of predictors considered in previous etiological studies and existing prognostic indices, it does not include variables available in other datasets that could inform mortality risk prediction among patients with dementia, namely, sociodemographic information (e.g., immigration status, race, education level, income quantile, rurality), functional status (e.g., activities of daily living, instrumental activities of daily living), and nutritional status (e.g., body mass index). The absence of these variables may limit the predictive accuracy of the model. However, including primarily variables in the DAD facilitates external validation of the model in other Canadian jurisdictions, wherein linkage between the DAD and other datasets is not readily possible. The tool may not be able to be implemented in healthcare systems outside of Canada if it is not currently possible to draw on data from a hospital’s data warehouse to enter into a prediction model. This limits its applicability outside of Canada.

Based on previous knowledge of the DAD, we expect that some prespecified predictor variables will have a high proportion of missing values (e.g., height and weight). We intend to pursue multiple imputation to infer missing values. However, should the values be missing not at random, then the variables may be refractory to multiple imputation and will be excluded from the model despite the possibility that they could inform mortality risk prediction in this patient population. Indeed, substantial missingness would suggest that the variables may not commonly be captured in the discharge summaries of hospitalized patients with dementia. Therefore, the inclusion of these variables in the model would limit its application. Finally, even if the analysis demonstrates acceptable performance of the model, it will require external validation to confirm its generalizability. Thereafter, implementation studies will be required to determine the potential impact of the tool on clinical decision-making, patient outcomes, and/or healthcare costs.

### Conclusion

A clinical prediction tool that provides personalized estimates of mortality among hospitalized patients with dementia has the potential to prompt advance care planning, increase access to primary and specialist palliative care, and ultimately, to facilitate receipt goal-concordant healthcare. Similar to the mHOMR, which has been implemented in several Ontario hospitals, this model could be integrated into electronic medical records as an automated tool for mortality risk prediction as soon as a patient with dementia is hospitalized, which could inform their care both during admission and upon discharge.

This model advances the work done by previous investigators by creating a population-level prognostic tool among hospitalized patients with dementia that is sufficiently complex to reflect the intricacies of mortality risk prediction in this patient population. The analysis plan will be informed by guidelines for regression modelling and clinical prediction models, and reporting of the model will adhere to the TRIPOD statement for multivariable prediction models for prognosis. Although the model will be internally (temporally) validated, it will require external validation and investigation of its potential impact on clinical decision-making, patient outcomes, and healthcare costs before implementation.

## Data Availability

The dataset used for this study will be held securely in a de-identified form at ICES. While data sharing agreements prohibit ICES from making the dataset publicly available, access may be granted to individuals who meet prespecified criteria for confidential access, available at www.ices.on.ca/DAS.

## Abbreviations

DAD: Discharge Abstract Database
mHOMR: Modified Hospital One-Year Mortality Risk
VIF: Variance inflation factor
